# Clinical and radiological effect of medialized cortical bone trajectory for lumbar pedicle screw fixation in patients with degenerative lumbar spondylolisthesis: study protocol for a randomized controlled trial (mPACT)

**DOI:** 10.1186/s13063-018-2504-z

**Published:** 2018-02-20

**Keywords:** Lumbar degenerative disc disease, Transforaminal lumbar interbody fusion, Cortical bone trajectory, Pedicle screw fixation, Minimally invasive technique

## Abstract

**Background:**

Spinal fusion with pedicle screw fixation represents the gold standard for lumbar degenerative disc disease with instability. Although it is an established technique, it is nevertheless an invasive intervention with high complication rates. Therefore, minimally invasive approaches have been developed, the medialized bilateral screw pedicel fixation (mPACT) being one of them. The study objective is to evaluate prospectively the efficacy and safety of the mPACT technique compared with the traditional trajectory for degenerative lumbar spondylolisthesis.

**Methods/design:**

This is a single-center, randomized, controlled, parallel group, superiority trial. A total of 154 adult patients are allocated in a ratio of 1:1. Sample size and power calculation were performed to detect the minimal clinically important difference of 10%, with an expected standard deviation of 20% in the primary outcome parameter, the Oswestry Disability Index, with power of 80%, based on an assumed maximal dropout rate of 20%. Secondary outcome parameters include the EuroQoL 5-Dimension questionnaire, the Beck Depression Inventory, the painDETECT questionnaire and the “timed up and go” test. Furthermore, radiological and health economic outcomes will be evaluated. Follow up is performed until 5 years after surgery. Major inclusion criteria are lumbar degenerative spondylolisthesis with Meyerding grade I or II, which qualifies for decompression and fusion by medialised posterior screw placement with cortical trajectory (mPACT) or by a traditional trajectory for lumbar pedicle screw placement.

**Discussion:**

This trial will contribute to the understanding of the short-term and long-term clinical and radiological postoperative course in patients with lumbar degenerative disc disease, in which the mPACT technique is used.

**Trial registration:**

ISRCTN registry, ISRCTN99263604. Registered on 3 November 2016.

**Electronic supplementary material:**

The online version of this article (10.1186/s13063-018-2504-z) contains supplementary material, which is available to authorized users.

## Background

Spinal fusion with pedicle screw fixation represents the gold standard of surgical treatment of lumbar degenerative disc disease (DDD) with instability of the spinal segment in recent years. Fusion is achieved by creating a firm osseous bridge between the affected levels. Thus, a cage that is inserted via the transforaminal route (transforaminal lumbar interbody fusion (TLIF)) is commonly used to restore the intervertebral disc and foraminal height [1]. Although pedicle screw fixation with transforaminal lumbar interbody fusion is an established technique, it is nevertheless an invasive intervention with high complication rates [2].

Regardless of the popularization of tube-based unilateral minimally invasive (MIS) approaches for TLIF, bilateral posterior exposure was not initially considered possible to be performed in a less invasive fashion. The introduction of the cortical bone trajectory for the placement of medialized bilateral pedicle screw and rod fixation (mPACT) has changed the requirement for wider exposure in posterior fusion and has led to the development of a further MIS posterior approach [3–5]. Although various reports on mPACT have been published recently, there are no randomized, controlled, prospective clinical trials with long-term follow up on this issue. Its application is determined predominantly by the individual surgeon’s preference and skill [3, 6, 7].

The study objective is to prospectively evaluate the efficacy and safety of medialized cortical bone trajectory for lumbar pedicle screw placement compared with the traditional trajectory for degenerative lumbar spondylolisthesis. Both surgical approaches are well-established techniques in clinical practice.

## Methods/design

### Study design

The mPACT study is a single-center, randomized, controlled, parallel group, superiority trial with 154 patients allocated to the groups in a 1:1 ratio. Any trial involving a surgical procedure precludes surgical investigators from being blinded. Patients, however, will be blinded to the randomized treatment and further evaluations, such as radiologic analyses, will be conducted in a blinded fashion whenever possible. The expected enrollment time is 2 years. The conclusion of the study is estimated 5 years thereafter. The primary study endpoint is the difference in Oswestry Disability Index (ODI) between treatment groups at 2 years after surgery. The ODI is a widely used tool for the assessment of therapeutic effect. It consists of ten sections, with six questions in each section. A lower score indicates a higher level of function. An overall score of all 10 sections of the ODI will be computed and used as the ODI score. The standardized version of the ODI can be computed by re-scaling the score to the range 0–100 [8]. Moreover, the generic health status is assessed with the EuroQoL 5-Dimension questionnaire (EQ-5D) [9]. The Beck Depression Inventory (BDI) is used as a multiple choice self-reported inventory for measuring the severity of depression and responsiveness to treatment [10]. To identify neuropathic pain components the painDETECT questionnaire (PD-Q) will be used [11]. Furthermore, with the “timed up and go” (TUG) test the physical ability of walking is objectively documented and quantified [12]. Preoperative and postoperative magnetic resonance imaging (MRI) of the lumbar spine is performed. The image protocols include sagittal and axial sequences, both T1 and T2 weighted, in all patients [13–17]. A computed tomography (CT) scan is routinely performed one year after the intervention to assess the overall fusion rate [18]. Pre-operative American Society of Anesthesiologists (ASA) grade staging might allow the identification of risk factors. Neurological status and the quality and quantity of current pain medication are documented. Operation time and time of hospitalization is recorded. Pain medication usage, including epidural injections and nerve block injections are documented. Quantitative sensory testing (QST) is performed to assess and quantify low back pain non-invasively [19]. Blood samples will be tested preoperatively and postoperatively for TNF-α, IL-6, C-reactive protein (CRP) and leukocytes [20]. Direct costs of hospital care and the indirect costs of follow-up treatment outside the hospital will be evaluated. Costs of surgery and hospitalization including duration of inpatient stay, costs of nursing, costs of medication and physiotherapy are assessed after discharge from the hospital, according to the hospital’s internal cost-estimate lists. Additionally, the indirect costs after hospital discharge including physiotherapy, rehabilitation centers, pain medications, medical consulting etc. are documented on a routing sheet. Postoperative care is not standardized in the study protocol and will be performed according to the standard of care for degenerative lumbar spondylolisthesis at the study site. Primary and secondary outcome parameters are outlined in more detail in Table 1. Ethics approval was attained at the local ethics committee. This study complies with the World Medical Association Declaration of Helsinki Ethical Principles for Medical Research Involving Human Subjects, 2008. The final report will follow the CONSORT 2010 guidelines and its extension to non-pharmacological interventions. The CONSORT checklist is attached as Additional file 1.

**Table 1 Tab1:** Primary and secondary outcome parameters

Outcome parameters	Assessments
Primary outcome parameter	Oswestry Disability Index (ODI) at 2-year follow up to measure degenerative lumbar spondylolisthesis-related disability [8]
Secondary outcome parameter	Questionnaire - Timed “Up and Go” test (TUG) [12] - Beck depression inventory (BDI) [10] - Changes in physical and mental health captured by the Short Form (SF)-12v2 [9] - Core outcome measure index (COMI) [30, 31], patient-orientated outcome questionnaire including - visual analog scale (VAS) for back and leg pain - patient’s satisfaction - work disability - social disability - Pain relief on 100-mm VAS for back pain and leg pain - PainDetect Questionnaire (PD-Q) [11] - EuroQoL 5-Dimension (EQ-5D) [9]
	Intraoperative - loss of blood (LOB) - amount of blood transfusion - operative time - length of wound incision - type of wound closure
	Various - duration of hospitalization - device-related complications - surgery-related complications - re-operations - adverse events (AE), severe adverse events (SAE)
	Health care contacts
	Pain medication usage
	Hospital costs
	Radiological evaluation - MRI [13–16, 32] - x-ray evaluation (antero-posterior, lateral, flexion and extension, standing for overall sagittal alignment and differences in lordosis) - CT scan (overall fusion rate, rate of radiological and/or symptomatic adjacent segment disease, rate of pedicle and/or cage system implant failures)
	Serum markers (CRP, leukocytes, TNF-α, IL-6)

The primary study endpoint is the difference in Oswestry Disability Index between treatment groups at 2 years after surgery

*MRI* magnetic resonance imaging, *CT* computed tomography, *CRP* C-reactive protein

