### Statistical analysis

Primary and secondary variables and their change from baseline will be summarized by treatment group. Endpoints will be analyzed as appropriate in dependence on the data distribution at a two-sided 0.05 level of significance. Detailed descriptive statistics will be provided for the data collected and 95% confidence intervals will be calculated for all relevant estimates. Measurements on the course of follow up will be analyzed by analysis of covariance (ANCOVA) or generalized model alternatives for categorical or semi-quantitative data. Additional covariates, such as baseline measurements, will be included in the model as appropriate. MRI parameters and variables to assess functional neurological status will be summarized descriptively. Imputation of missing data has not been planned. The primary analysis will follow as randomized. All values will be expressed as the mean and standard deviation.

Data are analyzed for normality by the Kolmogorov-Smirnov test. The Wilcoxon signed-rank test or the paired *t* test is used to analyze continuous paired data, while McNemar’s test is used for categorical data. The Mann-Whitney U test and unpaired *t* test, are used to perform group comparisons of continuous clinical outcome variables while the chi-square and Fisher’s exact test are used to analyze intergroup differences in categorized outcome variables and demographic characteristics (age, sex ratio, duration of symptoms, etc.), respectively. Statistical analysis will be performed after recruitment, one year postoperatively and after completion of the last visit of the study population at the specified time points. An interim analysis will be performed 6 and 12 months after recruitment and after completion of the last visit of the study population at the specified time points.

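### Table 1 lists hospital costs only, although the text also promises post-discharge costs, and the general test rule makes no exception for skewed costs

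*Protocol article*

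**What the plan says.** The abstract announces an economic component: "Furthermore, radiological and health economic outcomes will be evaluated". The Study design section of the protocol article then gives the scope: "Direct costs of hospital care and the indirect costs of follow-up treatment outside the hospital will be evaluated". Hospital costs come from the hospital's internal cost lists. For the period after discharge, it says that "the indirect costs after hospital discharge including physiotherapy, rehabilitation centers, pain medications, medical consulting etc. are documented on a routing sheet". The same section sends the reader to Table 1 for more detail on the outcomes.

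The only cost entry in Table 1 is "Hospital costs". Two resource-use entries stand beside it as separate outcomes, "Health care contacts" and "Pain medication usage". The table lists no post-discharge cost and no total cost.

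The Statistical analysis section sets a general rule: "Endpoints will be analyzed as appropriate in dependence on the data distribution at a two-sided 0.05 level of significance". It screens normality with the Kolmogorov-Smirnov test and names the Mann-Whitney U test and the unpaired t test for comparing continuous clinical outcome variables between groups. It does not mention costs. It also says that all values are reported as mean and standard deviation, with 95% confidence intervals for relevant estimates.

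**The concern.** There are two separate problems.

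The first is scope. The text covers costs inside and outside the hospital; the outcome table covers the hospital only. The Discussion section describes shorter hospital stay as one purpose of minimally invasive techniques. A hospital-only outcome picks up that expected saving but leaves out rehabilitation and other later care that could offset it.

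The second is the estimand. For costs, the quantity of interest is the arithmetic mean, because total spend is the mean times the number of patients. Cost data are usually right-skewed, so a normality screen will tend to point towards the rank test. A rank test asks whether a patient in one arm tends to cost less than a patient in the other. That question can have a different answer from the comparison of means when a few expensive courses carry much of the spend.

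**Working it through.** **Scope, from the text.** Study design: hospital costs and post-discharge costs are both evaluated. Table 1: hospital costs only. Both are current text, and one refers to the other for detail, so the mismatch needs no assumption.

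**Inputs for the numerical check.** The article gives no cost mean, spread or skewness, so there is no stated cost figure to reproduce. The arm size is 154/2 = 77; after the stated 20% loss, 77 × 0.8 = 61.6, about 62. The level is two-sided 0.05, so 2.5% in one direction. All cost figures below are assumptions. A lognormal cost with mean m and coefficient of variation c has σ² = ln(1 + c²) and μ = ln m − σ²/2.

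**Check 1: rank test against means, with a few expensive courses.** Routine cost has mean 14,000 (control) or 13,000 (mPACT). An expensive course adds 20,000 in 5% or 10% of patients respectively.
- Control mean: 14,000 + 0.05 × 20,000 = 15,000.
- mPACT mean: 13,000 + 0.10 × 20,000 = 15,000.

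Mean costs are therefore equal. Share of simulated trials in which Mann-Whitney is significant in favour of mPACT:

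| Routine CV | 77 per arm | 62 per arm |
|---|---|---|
| 15% | 51–53% | 43–44% |
| 25% | 17% | 15% |
| 40% | about 7% | about 6% |

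A Welch t test on the same data rejects, in either direction, in about 5%. If expensive courses occur in 12% of mPACT patients, the mPACT mean is 13,000 + 0.12 × 20,000 = 15,400, which is 400 dearer. At CV 15%, Mann-Whitney still favours mPACT in about 40% (34% at 62 per arm).

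**Check 2: rank test against means, lognormal costs with equal means of 20.** The median is 20/√(1 + c²): 20/√1.25 = 17.9 for c = 0.5, and 20/√2 = 14.1 for c = 1.0. Equal means with unequal spread therefore give unequal medians, and the rank test responds to that. Significant in favour of mPACT, 77 per arm:

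| CV control / mPACT | Mann-Whitney | Welch t |
|---|---|---|
| 0.5 / 0.5 | 2.4% | 2.4% |
| 0.8 / 0.8 | 2.4% | 2.4% |
| 0.3 / 0.5 | 19% | 3.5% |
| 0.5 / 0.8 | 27% | 3.9% |
| 0.4 / 0.8 | 45% | 4.6% |
| 0.5 / 1.0 | 55% | 4.9% |

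With the same shape in both arms the rank test holds its level. It departs only when the shapes differ.

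**Check 3: hospital cost against total cost.** Hospital cost is 13.5 (mPACT) against 15 (control), CV 0.3. Post-discharge cost is 6.5 against 5, CV 1.0. Totals: 13.5 + 6.5 = 20 and 15 + 5 = 20. For hospital cost alone, the standard error is √((4.05² + 4.5²)/77) = 0.69 and 1.5/0.69 = 2.17, so the chance of significance is about Φ(2.17 − 1.96) = 58%. Simulation gives 57% by Mann-Whitney and 58% by Welch t. A Welch t test of total cost favours mPACT in 2.9%. The scope problem therefore does not depend on which test is used.

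**The case against.** Several stronger readings are tempting, and the article does not support them.

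- *Post-discharge costs are excluded.* They are not. The Study design section says they will be evaluated and recorded, and Table 1 may simply use a short label. Health care contacts, pain medication, re-operations and complications are also listed there. What stands is that the more detailed list omits a cost that the text promises.
- *Costs are sent to a rank test.* This is an inference. The Mann-Whitney sentence concerns clinical outcome variables, costs are not named, and the t test is offered as well. The detailed cost analysis may sit in a full protocol or analysis plan that is not shown. What stands is that the general rule is worded for endpoints without exception, and hospital cost is a listed endpoint.
- *mPACT would be declared cheaper when it is not.* No section gives a rule for such a declaration. Means and standard deviations are to be reported, so a higher mean would be visible. The illustrations also need arms whose cost distributions differ in shape, or offsetting post-discharge costs. The article does not suggest that mPACT leads to more expensive courses; its Discussion cites greater pullout strength and rigidity. What stands is that the p-value and the reported means could answer different questions.
- *The term indirect costs misleads.* The article spells out what it means: "the indirect costs after hospital discharge including physiotherapy, rehabilitation centers, pain medications, medical consulting etc". This is a matter of terminology and changes no analysis.

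**Conclusion.** The point holds in a limited form. The mismatch between the Study design text and Table 1 is there on the page. The test-choice problem is conditional: it arises if the general distribution-driven rule is applied to costs and the arms differ in cost shape. Its size ranges from none (same shape in both arms) to about half of trials (51–53% with a routine CV of 15%, up to 55% in the most unequal lognormal case), always with equal true means and 77 per arm. At a routine CV of 40% it is about 7%, against a nominal 2.5% in that direction. Every one of these figures rests on assumed costs. They show what can happen and do not predict this trial. The outcome is secondary, and the ODI comparison at 2 years is untouched, so this is a minor point.

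**What to change.** 1. Align Table 1 with the Study design text: replace the hospital-only entry with hospital plus post-discharge care cost per patient up to a stated time (for example 2 years), including re-operations. Hospital cost can remain as a component.
2. Exempt costs from the distribution-driven choice of test. Compare arithmetic means between arms with a bootstrap 95% confidence interval, or use a gamma model that reports a contrast of means.

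The cost is a change of wording in Table 1 and in the analysis plan. The post-discharge items are already meant to be recorded on the routing sheet; the sponsor should confirm that it is kept up to the chosen time. The statistical price is a wider interval for total cost than for hospital cost alone.

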### Study population

The mPACT trial will include patients with lumbar degenerative spondylolisthesis of Meyerding grade I or II, who qualify for decompression and fusion of ≤ 3 lumbar spinal levels by a posterior medialized cortical bone trajectory or by a traditional trajectory for lumbar pedicle screw placement. These participants need to have failed adequate conservative or interventional therapy for a minimum of 3 months. Additionally, radiologically determined pathologic change at the treatment level needs to correlate with the primary symptoms. Patients with significant morbidities need to be excluded as this may lead to differences in treatment efficacy. Inclusion and exclusion criteria are described in detail in Table 2. Informed consent is obtained from each patient.

**Table 2 Tab2:** Inclusion and exclusion criteria

	Criteria
Initial inclusion criteria	Age between 18 and 85 years Clinical signs of low back pain and/or radiculopathy from vertebrae L1 to S1 MRI and CT confirmed: central canal stenosis, lateral recesses stenosis, or foraminal stenosis leading to: - radiculopathy, defined as pain and/or motor weakness or paralysis and/or paraesthesia in at least one specific nerve root distribution from vertebrae L1 to S1 or - neurogenic intermittent claudication, defined as pain and/or weakness and/or abnormal sensation in the legs during walking or prolonged standing or - indicating decompressive surgery and instrumented mono-segmental, bi-segmental or tri-segmental spondylodesis with posterior instrumented fusion system and an intervertebral cage (TLIF) Unresponsive to non-operative treatment for a minimum of 3 months including at least physiotherapy, pain medication and local infiltration therapy Presence of progressive symptoms or signs of nerve root and/or spinal cord compression although performing conservative treatment Psychosocial, mental and physical ability to understand and to perform with this protocol, especially visiting scheduled follow-up controls, observe treatment plan and all other study-related procedures Personally signed and dated informed consent document prior to any study-related procedures indicating that the patient has been informed of all pertinent aspects of the trial
Initial exclusion criteria	Previous surgery: (a) any instrumented lumbar spinal surgery, (b) cervical and/or (c) thoracic spinal disease to the extent that surgical consideration is likely or anticipated within 6 months after the lumbar surgical treatment Other degenerative joint diseases (i.e. shoulder, hip knee) to the extent that surgical consideration is likely or anticipated within 6 months after or before the lumbar surgical treatment Any other physical diseases (e.g. neuromuscular disorders) before and/or within 6 months after lumbar surgical intervention, which are able to restrict study procedures (i.e. wheelchair bound) or preclude accurate clinical examination or outcome Severe obesity (BMI >35 kg/m^2^) Neoplasia as the source of symptoms Fixed or permanent neurological deficit unrelated to the lumbar spine disease Active or chronic infection, systemic or local, including HIV, AIDS, hepatitis Active malignancy defined as a history of any invasive malignancy, except non-melanoma skin cancer, unless the patient has been treated with curative intent and there have been no clinical signs or symptoms of the malignancy for a minimum of 5 years Autoimmune disorder that impacts the musculoskeletal system (i.e. lupus, rheumatoid arthritis, ankylosing spondylitis) Acute episode or major mental illness (psychosis, major affective disorder or schizophrenia) Physical symptoms without a diagnosable medical condition to account for the symptoms, which may indicate symptoms of psychological rather than physical origin Recent or current history of substance abuse (drugs, alcohol, narcotics, recreational drugs) Known allergy to titanium, carbon/PEEK and tantalum or intolerance to any device material
Radiological exclusion criteria	Three or more vertebral levels requiring surgical treatment in the lumbar spine Clinically compromised vertebral bodies at the affected level due to current or past trauma, including osteoporotic fractures Spondylolisthesis according to Meyerding grade III or higher
Various exclusion criteria	Patient is currently pursuing personal litigation Pregnancy or the desire to become pregnant in the next year Prisoner or ward of the state Patient has used another investigational drug or device within the last 30 days prior to surgery

*MRI* magnetic resonance imaging, *CT* computed tomography, *BMI* body mass index, *PEEK* Poly-ether-ether-ketone

